**Original Trial Protocol and Statistical Analysis Plan**

Purpose of the Study

Objectives & hypotheses to be tested

The objective of this study is to determine how a Well-being Collaborative web-based seminar series, and online resilience tools, in full or in part, will impact individual well-being. Efficacy of the resilience sessions and tools will be assessed using psychometrically validated survey scales of burnout, depression, happiness, work life balance, disruptive behaviors, emotional thriving, emotional recovery, optimism and state-based anxiety.

The primary hypothesis is that the web-based series and tools will improve individual measures of burnout, depression, happiness, work life balance, disruptive behaviors, emotional thriving, emotional recovery, optimism and state-based anxiety when comparing pre-intervention and post-intervention matched data. We further hypothesize that individual improvements will have a spillover effect on aspects of the shared work environments including disruptive behaviors.

Background & Significance

Should support the scientific aims of the research

Burnout syndrome is a work-related psychopathology comprised of emotional exhaustion, cynicism and inefficacy, which occurs in professionals who do “people work.” Burnout develops from chronic exposure to interpersonal stressors – such as frequent interactions with individuals plagued by complex physical, psychological and social problems. Burnout is also perpetuated by unsupportive or inadequate work environments. Healthcare workers are uniquely vulnerable to burnout as the complex physical crises of patients are often accompanied by equally complex psychosocial and spiritual crises of the individuals and their families. Burnout has been associated with low job satisfaction, absenteeism, poor staff retention, low staff morale, poor performance, disturbed sleep, poor health outcomes and even higher all-cause mortality.

The prevalence and severity of burnout syndrome in healthcare workers is under-recognized as a significant factor affecting the quality and safety of care. The prevalence of burnout in healthcare workers ranges from 27-86%. More alarming is the correlation between burnout and sub-optimal patient care and medical errors. Despite the need for interventions to reduce healthcare worker burnout, few exist.

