The Looking Forward Tool asks participants to "Think about something you hope to experience or are looking forward to 3 years from now. ..." and describe what you are looking forward to in 3-4 sentences. Participants will be recruited by the same current method: learning about the tools in a continuing education offering or newsletter, and enrolling through a link on our website. Participants will complete baseline measures and be randomized to either begin the tool immediately (cohort 1), or wait 4 days to begin (cohort 2). Both groups will be assessed on day 4 (waitlist group/cohort 2 will be assessed before they begin the tool). Cohort 1 will continue on with the tool 3 more days; once initiated, the tool is 7 days total for both groups. The RCT comparison will assess treatment efficacy between 4 days of the tool (cohort 1) to the waitlist group (cohort 2). Both groups will be assessed at 1 and 6 month follow-ups for long term efficacy.

We also offer WISER through an observational arm, whereby investigators seek to optimize the number and sequence of WISER modules. The observational arm is intended to help us understand which components of WISER have the biggest and most enduring impact on well-being across different healthcare delivery settings, demographic groups, as well as which modules should be offered earlier in the series so as to maximize participation and improvement in well-being.

The full, condensed, and 4-day versions of WISER were created according to evidence-based principles of adult learning, combining educational material with practice-based learning. We demonstrate the need using evidence of the prevalence and severity of burnout, then the evidence regarding the efficacy of the specific tool being covered, then present the tool for practice-based learning.

Module content WISER condensed: The condensed version of WISER consists of pre-recorded videos, each under 10 minutes in length, playable during use of the tool. The videos are highly refined to be engaging, evidence based, and practical as a launch to the subsequent reflective activity using very brief and enjoyable applications of the module content.

Module 1. Thematic Introduction prevalence of burnout, evidence of enhancing resilience and overview of the next 6 modules.

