#### Individual Module Survey

The observational arm of this research does not use the entire pre-selected set and sequence of modules, but rather allows tools to be accessed individually. Unlike the full and condensed versions of WISER, this consists of briefer surveys pre and 1, 6, and 12 months post, and exclude spiritual climate items (taking participants approximately 8-10 minutes to complete).

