#### Selection of Subjects

List inclusion/exclusion criteria and how subjects will be identified.

Adults 18 and over are considered eligible for the study. A sub-sample will include employees (including but not limited to frontline caregivers, support staff and management) of the Duke University Health System, as well as external health systems. All participants will be invited to participate in one or more of the online tools. We will allow the participation of any clinical areas/healthcare worker groups whose leaders express interest in building resilience.

We are targeting healthcare workers for recruitment in the study, but adults 18+ are eligible to participate in any of these tools. Identification as a healthcare worker or not is part of data collection in every tool.

Adults who are not proficient in English, do not have basic computer skills, or who have prohibitive vision or hearing disabilities will be excluded from this study as they will be incapable of full participation in the intervention and/or the survey process. However, given the nature of their occupations we anticipate few, if any exclusions.

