### Subject Recruitment and Compensation

Describe recruitment procedures, including who will introduce the study to potential subjects. Describe how you will ensure that subject selection is equitable and all relevant demographic groups have access to study participation (per 45 CFR 46.111(a) (3)). Include information about approximately how many DUHS subjects will be recruited. If subjects are to be compensated, provide specific prorated amounts to be provided for expenses such as travel and/or lost wages, and/or for inducement to participate.

Potential participants may learn about the links to the WISER tools at a talk or workshop given by the researchers. They may also learn about them from word of mouth of someone attending one of these talks, or the website for the Duke Center for the Advancement of Well-being Science (<https://caws.dukehealth.org>). Talks include grand rounds, formal presentations for continuing education, and virtual presentations for continuing education credit. At Duke North, for example, this could be at Duke 2100, or for those logging in to watch it virtually while it's being given at Duke North 2100.

For the full WISER RCTs, managers and directors of targeted clinical areas, as described above, will be contacted via email and asked to attend the introductory webinar for managers and directors. Managers and directors may voluntarily spread the word about WISER to their work settings or in response to a follow up email after the introductory webinar.

We estimate that approximately 500,000 adults (18 or older as confirmed by their informed consent statement that they are 18 or older) will participate in the study. 10,000 participants are expected to work at Duke University Health System.

Attrition is a concern in behavioral interventions such as WISER. We will address attrition in several ways. (1) By offering an intervention that is fun, practical, and both personally and professionally transformative. (2) Minimizing any time commitment for participants, which is why we have shortened and edited the webinar/videos in a parsimonious yet appealing manner to allow for viewing at e.g., shift change. (3) Participants can claim continuous education credits for completing the modules. (4) Participants will receive personalized confidential feedback of their well-being metrics.

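### The observational arm's aims (best modules, number and order) go beyond its design: participants choose their tools, so tool and order differences are confounded with who chose them.

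*Protocol*

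**What the plan says.** The Resilience Collaborative Web-based Series section of the protocol sets three aims for the observational arm:

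- Number and order: "investigators seek to optimize the number and sequence of WISER modules".
- Comparative effect: to understand "which components of WISER have the biggest and most enduring impact on well-being across different healthcare delivery settings, demographic groups".
- Priority: to learn "which modules should be offered earlier in the series so as to maximize participation and improvement in well-being".

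The Individual Module Survey section describes how the same arm runs. It "does not use the entire pre-selected set and sequence of modules, but rather allows tools to be accessed individually", with shorter surveys before use and at 1, 6 and 12 months.

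Entry is voluntary and the number of tools is open. Selection of Subjects states: "All participants will be invited to participate in one or more of the online tools". Subject Recruitment and Compensation adds: "Potential participants may learn about the links to the WISER tools at a talk or workshop given by the researchers", and also names word of mouth and a website.

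On analysis, the primary hypothesis for the series and tools as a whole is an improvement "when comparing pre-intervention and post-intervention matched data". Data Analysis & Statistical Considerations names multi-level models, GLM and t-tests in general terms.

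**The concern.** Asking which module has the biggest impact, how many to offer and in what order is a comparative, causal question. An answer needs tool, number or order to vary independently of the participant's state and motivation. In this arm the participant decides which tools to take, how many and when, and no comparator is described.

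The arm's stated purpose is to guide which modules are offered and which come first. If its results are read as the aim is worded, those decisions could reflect differences between users rather than between tools. A large sample does not help: it narrows the interval around a confounded difference. The randomized comparisons elsewhere in the protocol are not affected.

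**Working it through.** **1. Aim against design.** The protocol states no effect size, SD, correlation or number of users per tool for this arm, so there is no figure to reproduce. The first check is whether any part of the protocol supplies the comparison that the aim needs.

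| Part of the protocol | What differs between groups | Compares tools, numbers or orders? |
|---|---|---|
| WELL-B randomized design | Start in week 1 or the following week, same four tools | No |
| Looking Forward randomized design | Start at once or after a 4-day wait, same tool | No |
| Full-format series | Topics listed in one chronological order | No, order is not varied |
| Observational arm | Participant's own choice | Only between self-selected users |

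The recruitment section also mentions randomized trials of the full series, but no design is given for them. So no randomized comparison of tools, numbers or orders is described.

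**2. Can a model repair this?** Take two tools with the same true effect. Let d be the baseline gap between their users (in SD) and r the pre-post correlation within each group. Both are assumptions. A higher score means worse.

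*Mechanism A: choice follows the observed baseline score, including its temporary part.*
- Expected gap at follow-up: r × d.
- Difference in raw change: r × d − d = −(1 − r) × d. The tool whose users start worse looks better.
- Difference after baseline adjustment: r × d − r × d = 0.

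*Mechanism B: users differ by a stable amount d.*
- Expected gap at follow-up: d.
- Difference in raw change: d − d = 0.
- Difference after baseline adjustment: d − r × d = +(1 − r) × d. The tool whose users start worse looks worse.

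The false difference has the same size in both cases, but it sits in a different model and has the opposite sign:

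| d | r | (1 − r) × d |
|---|---|---|
| 0.5 | 0.6 | 0.4 × 0.5 = 0.20 SD |
| 0.5 | 0.7 | 0.3 × 0.5 = 0.15 SD |
| 0.5 | 0.8 | 0.2 × 0.5 = 0.10 SD |

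Over d = 0.2 to 0.5 and r = 0.5 to 0.8 the range is 0.2 × 0.2 = 0.04 SD to 0.5 × 0.5 = 0.25 SD.

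Simulation agrees for both mechanisms. Under A (2,000,000 participants, r = 0.6, gap 0.30 SD), raw change differed by 0.12 SD and the adjusted difference was 0.001 SD. Under B (stable gap 0.5 SD, r = 0.6, 0.7, 0.8), raw change differed by about 0.00 and the adjusted model gave 0.20, 0.15 and 0.10 SD.

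**3. Sample size.** Under A with raw change, the variance of change is 2(1 − r). The number per tool at which a two-sided 5% test declares the false difference with 80% probability is 15.698 × 2(1 − r) / [(1 − r)d]², where 15.698 = 2 × (1.96 + 0.84)² before rounding.

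- d = 0.5, r = 0.5: 15.698 × 1.0 / 0.0625 = 252.
- d = 0.5, r = 0.6: 15.698 × 0.8 / 0.04 = 314.
- d = 0.2, r = 0.8: 15.698 × 0.4 / 0.0016 = 3925.

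The recruitment section expects about 500,000 adults in all. Users per tool are not stated, but counts of this order are conceivable.

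**The case against.** The strongest reply is that the arm is openly called observational and is meant to help the investigators understand, which permits an exploratory reading. It is separate from the primary hypothesis and from the randomized designs. Covariates may be specified in an analysis plan that is not at hand, and the named methods could carry them. Part of the aim concerns participation, and on that the tools people choose and finish are direct, though not conclusive, evidence.

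Much of this stands. The missing covariate list is no finding, and the participation part of the aim can stay. But optimizing number and order, and naming the components with the most impact, go beyond an exploratory description.

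A reader might also infer four stronger points, which the protocol does not support:

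- *Tools will be ranked on raw change.* No section says so. The matched pre-post contrast is the hypothesis for the series and tools overall.
- *Tools on grief or burnout will draw people with worse scores.* The module descriptions explain the exercises and give no baseline data.
- *There is no order to analyze.* The protocol drops only the pre-selected sequence. People who use several tools create their own order, which is confounded but exists.
- *Baseline adjustment cures the problem.* It does so only under mechanism A. The Resilience Collaborative Survey section says that the enrollment links contain the pre-intervention questions. If tool links work this way, the tool is chosen before the score is measured, and mechanism A cannot be taken for granted.

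**Conclusion.** The point holds as a mismatch between aim and design. Comparative conclusions about tool, number and order are to be drawn from an arm in which participants choose their tools, and the protocol describes no randomized comparison that could supply them. This rests on the text alone.

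The size is unknown. The 0.04 to 0.25 SD range is an illustration that depends on an assumed baseline gap, an assumed correlation and the selection mechanism. If users of different tools do not differ, there is no such bias; if they differ only in stable level, raw change is free of it and the adjusted model is not. Motivation, attrition and carry-over from earlier tools would add to the confounding, and neither model deals with them. The consequence is limited to this arm's conclusions.

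**What to change.** In the Resilience Collaborative Web-based Series section:

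1. Reword the aim of the observational arm to describe uptake, completion and change in well-being among people who chose each tool.
2. Label any comparison between tools, numbers of tools or orders as exploratory and associational, whichever model is used.
3. State that no conclusion on the most effective tool, or on the optimal number or sequence, will be drawn from this arm.

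This costs a few sentences and needs no new data. The small downside is a weaker claim. If a firm answer on tool or order is wanted, it needs a design that randomizes them, which is a larger undertaking than this rewording.

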### Resilience Collaborative Survey

A pre-intervention survey will be administered prior to the first webinar and post-intervention surveys will be administered following the last webinar and again 1, 6, 12, 18, and 24 months later. The pre and post surveys will be nearly identical and consist of demographic variables (e.g. healthcare system, clinical area, position, years of experience, gender, and shift), a 5-item version of the Emotional Exhaustion dimension of the Maslach Burnout Inventory, the Center for Epidemiological Studies Depression Scale-10-item version (CES-D10), the Subjective Happiness Scale, the Work-Life Activities and Behaviors Questionnaire ([name]), Optimism (LOT-R), Anxiety (GAD-7) and Emotional Thriving and Emotional Recovery. Additional unpublished spiritual climate items, turnover intention items, and items pertaining to vacation time, will be asked as well. The pre- and post- intervention surveys will take participants approximately 15 minutes, or less, to complete.

In addition to the pre- and post- intervention surveys, brief peri-intervention surveys will be administered during each webinar. The purpose of the peri-intervention surveys are to ascertain whether individuals absorbed the main concepts of the webinar and to evaluate the efficacy of specific interventions shared during the intervention (e.g. the three good things exercise).

A separate continuing education (CE) survey to evaluate participant attendance and course content in order to award participants continuing education credit will be sent at the end of the module content (prior to refresher webinars). Credit will be offered and awarded in the form of IACET Continuing Education Units (CEUs) to all participants who complete the study. The names of participants who complete the CE survey will be shared with the CEU office.

CEUs may be considered an incentive for attending the webinars, however there is no requirement that healthcare workers participate in the research component of this study to be awarded CEU credit.

Participation will be voluntary and surveys will be administered electronically to maintain confidentiality. Qualtrics Survey Research Suite will be used to distribute, collect and store survey data. Enrollment links that contain the pre-intervention survey questions are available on our website, newsletter, and during continuing education sessions as part of the slides. Those individuals who wish to participate in the research will complete the consent form which is followed by the pre-intervention survey. Those who wish only to participate in the continuing education credit component will be asked for their email address, and these records used solely for the purpose of awarding continuing education at the end of the series. Those who do not wish to participate in either the research or the continuing education opportunity will not be asked to enter any additional information, and thus the study team will have no record of identifying information for these individuals. Research subjects who initially consent to the research study may request to have their email address removed from our study list serve at any time, in response to any electronically mailed survey. There is an “opt out” link in every survey sent to participants. Longitudinal survey data will be collected from each participant and matched using a unique study number created for each participant by the Qualtrics survey software. The pre-intervention survey is the only survey which will ask respondents for a unique identifier (email address), as this is necessary for follow up. Subsequent survey data files will only contain the unique study numbers of each participant. The data from the pre-intervention survey will be removed from the Qualtrics database within 3 months of collection and study personnel will remove the email address identifiers from the dataset at this time and prior to analysis. All data files, once removed from Qualtrics, will be stored on the encrypted study computers for at least 6 years following the completion of the study. Survey results, once matched, will be analyzed in aggregate by clinical area or healthcare worker group. Clinical areas or healthcare worker groups with less than 5 respondents will be excluded from the analysis to ensure responses of individual participants cannot be identified. Participants may choose not to respond to any of the surveys or specific survey questions, or may withdraw from the study at any time.

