## Resilience Collaborative Web-based Series

The Resilience Collaborative Web-based series is a condensed version of the two day “Enhancing Caregiver Resilience: Burnout & Quality Improvement Course” offered by the Duke Center for Healthcare Safety and Quality since 2009. The webinar series is commonly referred to as WISER, short for Web-based Implementation for the Science of Enhancing Resilience. WISER is offered in three formats, full, condensed, and 4-day. The full format of WISER consists of either 12 or 24 webinars, approximately 60 minutes in length each. The condensed format of WISER consists of 10 minute pre-recorded videos using the same content, just offered in smaller chunks. For work settings that afford little logistical opportunity to watch an hour-long video, like NICUs or busy primary care

practices, the condensed format of WISER is recommended. For work settings that have continuing education windows or more logistical flexibility, the full format of WISER is recommended. The most recent version, the 4-day format of WISER, involves 4 consecutive days of 1-hour live or recorded webinars.

WISER is also offered via a randomized control trial design to assess the 5-day format. This format, called WELL-B, introduces participants to a subset of topics in the full WISER format- specifically four of the WISER tools, 1 per day (i.e., Work-life balance, Gratitude, Self-compassion, and Awe). This RCT will occur in the context of a 5 day webinar training. Enrollees will be randomized during electronic informed consent in Qualtrics to either cohort 1 (M-Th) or cohort 2, which occurs the following week (M-Th) via webinar. For those assigned to cohort 1, assessments will occur the first day of the training and day 8 (1-week after the training) as well as 1, 6, and 12 month follow-ups. For those assigned to cohort 2, assessments will occur on their first day of training (day 8 of cohort 1), 1 week after the training, and at 1, 6, and 12 month follow-ups. The RCT comparison will assess tool efficacy between the cohort 1 (week 1) and cohort 2 (week 2). Follow-ups will examine the long term efficacy of the tools.

Another randomized control design of WISER will specifically look at the "Looking Forward" WISER tool.

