## Data Analysis & Statistical Considerations

Describe endpoints and power calculations. Provide a detailed description of how study data will be analyzed, including statistical methods used, and how ineligible subjects will be handled and which subjects will be included for analysis. Include planned sample size justification. Provide estimated time to target accrual and accrual rate. Describe interim analysis including plans to stop accrual during monitoring. Phase I studies, include dose escalation schema and criteria for dose escalation with definition of MTD and DLT.

There are approximately 5000 health care workers working within fewer than 300 clinical areas nested within the participating healthcare systems. Multi-level modeling will be used to account for nesting, while descriptive statistics, GLM, and T-tests will be used to explore distributions and relationships. The three good things logs will be analyzed using linguistic analysis software.

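### A confidentiality safeguard is written as an analysis exclusion: units with fewer than 5 respondents leave the analysis, with no stated limit to by-unit results and no survey wave named

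*Protocol*

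**What the plan says.** The rule is in the protocol, section Resilience Collaborative Survey: "Clinical areas or healthcare worker groups with less than 5 respondents will be excluded from the analysis". The purpose follows in the same sentence: "to ensure responses of individual participants cannot be identified". The sentence immediately before reads "Survey results, once matched, will be analyzed in aggregate by clinical area or healthcare worker group".

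Other sections describe analyses at the level of the person:

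- The primary hypothesis, under Objectives & hypotheses, concerns individual measures "when comparing pre-intervention and post-intervention matched data".
- Data Analysis & Statistical Considerations states "There are approximately 5000 health care workers working within fewer than 300 clinical areas nested within the participating healthcare systems", and then "Multi-level modeling will be used to account for nesting". It does not repeat the under-5 rule and does not set it aside.
- Resilience Collaborative Web-based Series describes two trials that randomise individuals. For WELL-B, "Enrollees will be randomized during electronic informed consent in Qualtrics to either cohort 1 (M-Th) or cohort 2". For the Looking Forward tool, people complete baseline measures and are then allocated to start at once or after 4 days.

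The survey section also says that surveys and single questions may be skipped, that data are matched by study number, and that email addresses are taken out before analysis.

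**The concern.** Preventing identification calls for a limit on what is shown. A score that enters a pooled or multi-level model is not revealed by doing so; a printed result for a unit of three people might be. The rule as worded acts on the analysis itself.

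Three things are at stake.

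1. **Precision and representativeness.** Whether a person is analysed depends on how many colleagues answered and on how large the unit is. A unit with four or fewer staff fails even if all of them respond. Single enrollees from outside systems are likely to fail, and adults who are not healthcare workers, who are eligible under Selection of Subjects, have no evident area or group.
2. **The randomised sets.** If the rule reaches the two trials and respondents are counted after baseline, randomised people are removed because of something that happened after allocation.
3. **Ambiguity.** Two analysts could apply the sentence at different waves, or to areas in one case and worker groups in the other, and obtain different analysis sets.

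**Working it through.** The protocol gives no response rate, no spread of area sizes and no expected number of exclusions, so there is no figure of its own to reproduce. What follows is an illustration.

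**Input from the protocol.** About 5000 workers in fewer than 300 areas: 5000/300 = 16.7 per area. Because there are fewer than 300 areas, 16.7 is the smallest mean consistent with the text. With 200 areas, for example, the mean is 5000/200 = 25.

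**Assumptions.** Response r of 20%, 40% or 60%, independent within an area. Area sizes are either all equal to 17, or gamma-distributed with coefficient of variation (CV) 0.5 to 1.0. Only areas are modelled, since the protocol does not say how areas and worker groups combine under the rule.

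**Formula.** With X respondents in an area of size m, X ~ Binomial(m, r). The share of respondents discarded is the sum of x·P(X = x) over x = 1 to 4, divided by m·r.

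**Equal areas, m = 17.**
- r = 0.4: (1×0.0019 + 2×0.0102 + 3×0.0341 + 4×0.0796) / 6.8 = 0.443/6.8 = 6.5%. The chance that an area falls below 5 is 12.6%.
- r = 0.2: (1×0.0957 + 2×0.1914 + 3×0.2393 + 4×0.2093) / 3.4 = 2.034/3.4 = 59.8%. The chance of falling below 5 is 75.8%.
- r = 0.6: 0.1% lost. The chance of falling below 5 is 0.3%.

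**Unequal areas.** The same share, by simulation over gamma-distributed sizes:

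| Assumed area sizes | 20% response | 40% response | 60% response |
|---|---|---|---|
| Mean 16.7, CV 0.5-1.0 | 34-49% lost | about 14% | 4-7% |
| Mean 25, CV 0.5-1.0 | 20-26% | 4-7% | 1-4% |
| All areas 17 | 60% | 7% | 0.1% |

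**Cost in precision.** Treating respondents as independent, the standard error grows by 1/√(1 − share lost). For mean 16.7: at 60% response, 1/√0.96 to 1/√0.93 = 1.02 to 1.04; at 40%, 1/√0.86 = 1.08; at 20%, 1/√0.66 to 1/√0.51 = 1.23 to 1.40. Correlation within areas would alter these figures.

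**If the rule applied only to display,** the loss from the individual-level analyses would be zero in every cell of the table.

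**The case against.** The strongest reply is that the sentence must be read with its neighbour. The text has just described an aggregate analysis by area or worker group, so the analysis from which small units are excluded is naturally that one, and the confidentiality reason fits it. On this reading the protocol already does most of what is asked. The reading is fair and may be what was intended. But the sentence does not say so, and no other section confirms it, so the need for clarification stands.

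A reader might infer that the protocol removes randomised participants from the two trials. The document does not establish this. The rule stands in a survey section whose schedule (after the last webinar, then 1, 6, 12, 18 and 24 months) differs from the schedules of WELL-B and Looking Forward, and neither trial's comparison is described as being by area. Against that, both trials are described under the same web-based series, Subject Recruitment and Compensation speaks of WISER RCTs recruited through managers of clinical areas, and nothing exempts them. Coverage is an open question.

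A reader might also infer that the count is a post-baseline event. No wave is named. The reference to matched results hints at a later count, but a baseline count is possible; in Looking Forward, baseline comes before randomisation. A baseline count pooled over both cohorts would remove whole areas from both arms together, which costs precision and generalisability more than balance between arms.

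Finally, a reader might infer that the most burned-out units are the ones lost. The protocol gives nothing on how response relates to burnout, so neither the direction nor the size of a bias can be claimed.

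**Conclusion.** The point holds as a defect of wording with possible consequences for the analysis. A rule justified only by confidentiality is expressed as exclusion from analysis, without a stated scope and without a counting wave. Followed literally, it conflicts with an individual-level primary hypothesis and is unnecessary for a multi-level model, which can use clusters of any size. It adds little or no protection beyond withholding small-unit results.

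The loss ranges from negligible (0.1% with equal areas of 17 at 60% response) to more than half of respondents (60% with the same areas at 20% response). Everything except the 16.7 minimum mean is assumed, so no single figure should be quoted as the expected loss. Removal of randomised people on a post-randomisation event follows only if the rule covers the trials and the count is taken after baseline. Severity is moderate: the size is conditional and a harmless reading exists, but the remedy is cheap and should be in place before analysis.

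**What to change.** Replace the sentence with:

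> All respondents are included in the individual-level and multi-level analyses and in the randomised comparisons. Results for any clinical area or healthcare worker group with fewer than 5 respondents are not displayed separately and appear only in pooled results or a combined category.

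Add the survey wave at which the 5 are counted for display.

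The cost is a short protocol amendment; results for small units remain withheld in every report. One check is needed first: the new wording must agree with the confidentiality statement given to participants. That statement is not in the material at hand. If it promised that small units would not be analysed at all, the two texts have to be reconciled.
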